## Abstract

Reactive balance, a critical automatic movement pattern in response to a perturbation, is directly linked to fall prevention in older adults. Various exercise interventions have been broadly performed to improve reactive balance and thus prevent falls. Curiously, aquatic exercises have been suggested as an effective balance intervention and a safer alternative to exercises on dry land yet the efficacy of aquatic exercises on reactive balance has not been formally investigated. The present clinical trial aims to identify if skills acquired during aquatic exercise are more effectively transferred to a reactive balance task than land exercise. This study is designed as a double-blinded, randomized controlled clinical trial. Forty-four older adults aged 65 years or above who meet the eligibility criteria will be recruited and randomized into an aquatic exercise group or land exercise group. Each group will participate in the same single bout intervention that includes a ball throwing and catching task. A modified lean-and-release test will be implemented on land immediately before, after, and one week after the single bout intervention. The outcomes will include reaction time, rapid response accuracy, and mini-BESTest scores obtained from stepping and grasping reactions. All statistical analyses will be conducted using an intention-to-treat approach. Our conceptual hypothesis is that participants in the aquatic exercise group will demonstrate more improved outcome scores in the lean-and-release test when compared to those in the land exercise group. The results of the present study are expected to provide evidence to support the benefits of aquatic exercises for improving reactive balance in older adults. Further, participants may find aquatic exercises safer and more motivating, thus encouraging them to participate in further aquatic exercise programs.

## Introduction

### Background

In daily life, reactive balance control strategies are required in response to a variety of postural perturbations, such as slips, trips, or bumps (pushes or pulls), to avoid potential falls while sitting, standing, or walking. According to WHO Global Report on Falls Prevention in Older Age, risk factors associated with physical environments (e.g., slippery surfaces, unmarked obstacles, and uneven sidewalks) play the most significant role in falls in older adults [1]. Reactive balance, which can be defined as an ability to recover a stable postural balance in response to a mechanical perturbation, requires the rapid generation of postural muscles in the trunk, lower, or upper limbs to induce proper reactions, such as swaying around the ankle or hip joints, taking a reactive step, or reaching to grasp a handhold [2]. Delayed and inappropriate generation of corrective forces from the postural muscles may result in falling and injuries [3]. Reactive balance control is supported by visual, vestibular, or somatosensory feedback, and it can be improved by repeated exposure to perturbations not only in healthy young and older adults, but individuals with neurological diseases, such as multiple sclerosis [4].

### Ball throwing and catching exercise

In various clinical settings, exercises using ball throwing and catching activities have been broadly used to improve balance, gait, or proprioceptive functions and to reduce the risk of athletic injuries [5,6]. However, the number of balance exercise studies that utilize ball throwing and catching activities is limited, and there is still a need for further investigation of the effects of the activities on various balance outcomes. Ball throwing and catching exercise engages two different motor tasks, including targeted grasping reactions as a primary motor task and postural shifts as a secondary motor task, in conjunction with cognitive demands regarding perceptual processing of the direction of the ball projection. Activities of daily living generally necessitate balance control during one or more different tasks, thus, it has been identified that deteriorated balance control during dual-task testing is associated with future fall risk in older adults [7]. Several researchers have recently conducted balance exercise studies in healthy young adults [8], healthy older adults [9,10], older adults with mild cognitive impairment [11], stroke patients [12], and multiple sclerosis patients [13] using self-initiated or external postural perturbations to improve reactive balance, described as compensatory postural adjustments. They utilized a ball throwing activity as a self-initiated, internal postural perturbation and a ball catching activity as an external perturbation. The ball throwing and catching exercises improved both anticipatory and compensatory postural adjustments in the aforementioned populations, which was demonstrated by early onsets of postural (i.e., leg and trunk) muscle activities, larger anticipatory center of pressure (COP) displacements, and smaller compensatory COP and center of mass (COM) displacements. However, the participants, specifically the older adults or those with neurological diseases, in the studies were exposed to potential risks, such as losing balance and falling during the intervention and testing sessions conducted in a dry-land environment.

### Aquatic exercise

Exercises performed in an aquatic environment have been suggested as an effective alternative to exercises on dry land for people with a variety of clinical conditions as it offers a safer environment if one were to fall [14,15]. The effectiveness of aquatic exercise (AE) is fundamentally attributed to the physical properties of the water [14]. For example, the buoyancy of the water provides a supportive force and a reduction in joint loading. Viscous force and hydrostatic pressure enhance sensory and proprioceptive awareness, which may be beneficial to the postural control system [16]. In addition, the aquatic environment slows movements and enhances participants’ confidence level (i.e., decrease in fear of falling) by potentializing their ability to attempt movement outside their base of support [16]. Given these advantages of the aquatic environment, aquatic exercises have been widely implemented in the early stages of rehabilitation or used as a paradigm of aquatic cross-training [16,17]. Further, aquatic exercises are specifically advisable for those who cannot tolerate land-based exercises or strive for novel training stimuli.

The dynamic systems theory provides some additional justification to examine if an aquatic environment may confer some advantages over the land environment for improving reactive balance in response to a ball throwing and catching exercise. According to the dynamic systems theory, variability in the movement systems affects each individual’s behavior and consequently helps one adapt to ever-changing constraints (personal, task-related, or environmental) [18]. For example, gait training with a specific perturbation carries over to post-perturbation performance during walking [19]. The aquatic environment appears to increase the variability in movement behavior and therefore requires our neuromuscular system to adapt to it [20–23]. In general, less-skilled performers (e.g., older adults) or individuals with a certain disease, illness, or injury demonstrate diminished ability in utilizing appropriate biomechanical degree of freedom and consequentially weakened adaptability to task constraints [18]. Thus, for these populations, exercise interventions in an aquatic environment may be more effective at improving post-intervention performances regarding reactive balance in various circumstances versus those in a dry-land environment. Despite the abovementioned attributes and benefits of the aquatic environment, there is a void in the literature regarding how effectively aquatic exercises can be transferred to different tasks in a dry-land context when compared to land exercises.

### Problem statement

Specificity of training is a key element in improving balance, and it is particularly emphasized in perturbation-based reactive balance exercise interventions [24]. Thus, results from the abovementioned studies utilizing ball throws and catches as postural perturbations are noteworthy in that all of the results showed improvements in similar tasks [8–13], and three of which additionally demonstrated the transfer of the learning effects of the exercise interventions to another task, that was not a part of the interventions, but sharing the same directional specificity [9,10,13]. The number of perturbations and contexts that can be furnished during exercises is limited in conventional clinical or research settings. Hence, there is a need for further research to investigate the effectiveness of exercises that are broadly implemented in various clinical settings without environmental constraints on reactive balance.

In this study, reactive balance will be assessed using a modified lean-and-release test [25]. During the test, there are two options that participants can take, including reactive stepping and reach-to-grasp reaction, to avoid a fall. Moreover, cognitive processes are required to override a prepotent action (i.e., response inhibition) and select a suitable response (i.e., action selection) considering the available environmental affordances and constraints. A ball throwing and catching exercise in the current study will introduce these aforementioned components. While the previous studies included fixed-support reactive balance exercises and assessments, the single bout intervention in this study will require both fixed-support and change-in-support strategies. Both the test and exercise require eye-foot coordination (i.e., stepping) and/or eye-hand coordination (i.e., reach-to-grasp and ball catch) based on the environmental affordances, and participants will be required to maintain balance to avoid a fall after each reaction. Additional cognitive processes will be demanded via deceptive actions. The directions of the ball will be random, and some trials will include a deceptive action before the actual throw thus forcing a need for rapid response inhibition and action selection when they shift and catch the ball. During the single bout intervention, both the speed and accuracy of the movement will be emphasized.

Hence, the current study aims to compare measures of reactive balance control after a single bout intervention on land and in chest-deep water. There have been several studies presenting greater enhancements in dry-land balance performance, specifically in static and proactive balance measures, such as Berg Balance Scale [26], 8-Foot Up and Go Test [27], and Functional Reach Test [28] following AE versus land exercise (LE) in healthy older adults. As none of the previous trials included any measures of reactive balance, the current study will specifically focus on improvements in reactive balance capacity after a single bout intervention. During aquatic exercises, water resistance produces overload during movements, and hydrostatic pressure constantly facilitates sensory awareness and motor functions. Further, the confidence level is augmented in the safer aquatic environment, which in turn increases variability in movement systems and maximizes neuromuscular adaptations. Thus, we hypothesize that participants in an AE group will present greater improvements (e.g., more accurate and rapid responses) during the reactive balance assessment compared to those in a LE group. The greater improvements will be demonstrated by faster response speed (i.e., shorter reaction time), greater accuracy alongside faster response speed (e.g., higher rapid response accuracy), and greater quality of response (e.g., higher mini-BESTest score). The Mini Balance Evaluation System Test (mini-BESTest) is a comprehensive clinical balance assessment, which evaluates four different balance control systems. This tool is commonly used by clinicians and practitioners and well known to be advisable to identify the disordered systems underlying balance control and design specific rehabilitation approaches in varied age and patient populations [29]. In this study, the second section (Reactive Postural Control) will be utilized to score the quality of compensatory balance responses.

## Materials and methods

### Study design and setting

This study will be a double-blinded randomized controlled trial, implemented in the Sorenson Legacy Foundation Center for Clinical Excellence at Utah State University (Logan, Utah, United States). The protocol was designed in accordance with Standard Protocol Items: Recommendations for Interventional Trials (SPIRIT) statement (S1 Appendix) [30] and will be reported according to the Consolidated Standards of Reporting Trials (CONSORT) recommendations [31]. The trial results will be disseminated at national and/or international academic conferences and in peer-reviewed journals.

### Participants

A total of 44 individuals aged 65 years or above will be asked to participate in this study. Participants will be recruited from university and community settings via written flyers or word-of-mouth referrals. When a participant expresses interest in the study by contacting one of the researchers via the email address listed on the flyer, we will send a copy of the consent form via email to allow the prospective participant the opportunity to read the consent form and become fully informed before participating in the study. The estimated amount of time between first receiving a copy of the consent form and signing it in person at their appointment will be approximately one week.

Participants will be included in the study if they: 1) have the ability to stand using a double-leg stance for one minute of time, 2) walk independently, 3) have normal or corrected to normal vision, and 4) normal or corrected to normal hearing based on a qualitative assessment. Exclusion criteria will include: 1) any neurological or musculoskeletal disorders that may inhibit the participation in the single bout intervention and testing protocols; 2) a concussion within the past one year before the participation; 3) any cognitive deficiencies (e.g., memory, concentration, or attention disorder); 4) one or more ‘yes’ answered on the Physical Activity Readiness Questionnaire (PAR-Q); or 5) fear of water. To fully assess each participant’s eligibility, a pre-screening questionnaire will be additionally completed.

### Sample size calculations

A power analysis was conducted using G*Power software package (Version 3.1.9.7, Kiel University, Germany). Using results from previous work [26], an a-priori power calculation (α = 0.05, and 1-β = 0.80) determined that 38 participants (19 per group) will be required to determine significant intergroup differences based on large effect size (Cohen’s d > 0.8). Berg Balance Scale (BBS) score data from an AE and LE group were extracted for the analysis as (1) there was no study comparing the effects of AE and LE on any measures of reactive balance and (2) BBS is commonly considered to be the gold standard in testing functional balance and measuring fall risk in older adults [32]. Considering an approximately 15% dropout rate, a total of 44 participants (22 in each group) will be expected to enter the study.

### Ethical approval and registration

The procedures described in this protocol conform to the principles outlined in the Declaration of Helsinki and received approval from the Institutional Review Board at Utah State University (IRB: 12227). All participants will read and sign a written informed consent approved by the Institutional Review Board at Utah State University before participating in the experimental procedures. The protocol was registered on the U.S. National Library of Medicine (ClinicalTrials.gov) with the identifier (NCT05107817) on 3 November 2021. The individual in this manuscript has given written informed consent (as outlined in PLOS consent form) to publish these case details.

### Timeline

The process of enrollment, allocation, follow-up, and analysis are outlined in Fig 1. The participant recruitment is expected to continue from December 2021 to December 2022.

**Fig 1 pone.0275733.g001:**
[figure not shown]
CONSORT flow diagram of the planned protocol timeline.

### Randomization and allocation concealment

An experimenter, a certified athletic trainer, will screen according to the aforementioned eligibility criteria using a pre-screening medical history questionnaire and PAR-Q. Following the baseline screening, all participants meeting the eligibility criteria will be randomly assigned to either AE or LE group. Simple randomization will be applied using Random Allocation Software [33]. The numbers associated with the allocation sequence and identities will be kept in sealed envelopes and concealed until completion. Randomization and allocation will be implemented by an independent researcher not involved in any part of the study.

### Blinding

Participants and an assessor who will collect the outcome measures at the baseline, post-intervention, and follow-up and analyze the data will be blinded to the allocation. It will be impossible to fully blind the exercise instructors due to the nature of this study and their active role in the single bout intervention.

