### Intervention

The AE will be executed in a climate-controlled aquatic research laboratory, and the LE will be performed in a motion analysis laboratory. During AE, participants will stand barefoot on an adjustable floor of an aquatic treadmill (HydroWorx 2000TM, Middletown, PA), and the water depth will be adjusted to each participant’s xiphoid process level. Participants will sit on a chair for five minutes before AE for environmental acclimatization.

Participants will engage in a single bout intervention consisting of 120 repetitions of a ball throwing and catching task using a volleyball (Wilson Sporting Goods Co., Chicago, IL, USA). This single-session approach was selected based on a previous study, reporting the long-lasting effects of a single bout intervention with an intense reactive balance exercise [34]. Several previous studies also demonstrated that reactive balance in response to a postural perturbation has been improved after a single bout intervention [8,9,11–13].

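### The trial is called double-blinded with participants blinded to allocation, but participants know whether they exercised in water or on land; only the assessor/analyst and the video raters can be blinded

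*Protocol article*

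**What the plan says.** The Abstract states: "This study is designed as a double-blinded, randomized controlled clinical trial". Study design and setting repeats it: "This study will be a double-blinded randomized controlled trial".

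The Blinding section says who is meant: "Participants and an assessor who will collect the outcome measures at the baseline, post-intervention, and follow-up and analyze the data will be blinded". The sentence goes on to make clear that it is the allocation to which they are blinded. The same section makes one exception: "It will be impossible to fully blind the exercise instructors due to the nature of this study".

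The Problem statement describes the comparison as one of reactive balance "after a single bout intervention on land and in chest-deep water". The Intervention section adds: "The AE will be executed in a climate-controlled aquatic research laboratory, and the LE will be performed in a motion analysis laboratory". It also says: "During AE, participants will stand barefoot on an adjustable floor of an aquatic treadmill", with the water set at each participant's xiphoid level.

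On timing, Randomization and allocation concealment states: "Following the baseline screening, all participants meeting the eligibility criteria will be randomly assigned to either AE or LE group". Outcome measurement places the pre-test immediately before the bout, a second test immediately after it, and a third one week later.

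**The concern.** The two arms do the same ball task and differ in where they do it. A person standing in chest-deep water cannot be unaware of it, so the statement that participants are blinded to allocation describes a property the design cannot have.

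What is at stake is how the results are read. A reader who sees the double-blinded label and the Blinding section will assume that participants' expectations were balanced between arms by concealment. They are not. The article's own rationale makes this relevant. It gives greater confidence in water as part of the reason for expecting a benefit, and it describes the lean-and-release test as requiring response inhibition and action selection, so performance is not purely reflexive. A difference between arms at post-intervention or follow-up could therefore include an expectation component, and the label suggests that this has been excluded.

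**Working it through.** The article gives no figure on this point, so the check compares its statements.

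1. **What is claimed.** The Abstract and Study design and setting give the label. The Blinding section names participants and the assessor/analyst as blinded, and names allocation as what they are blinded to.

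2. **What allocation consists of.** The Problem statement and the Intervention section define it as land or chest-deep water, delivered in two different laboratories. No sham immersion and no masking of the environment is described.

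3. **Whether the claim can hold, role by role.**
   - *Participants:* not from the start of the session. Being in the water, or not, is the allocation.
   - *Exercise instructors:* no, and the article says so, citing the nature of the study. The same reasoning applies to the person being instructed, but the article does not extend it.
   - *Assessor/analyst:* feasible. All testing is on land with the same apparatus in both arms.
   - *Two video raters:* feasible. The Outcome measurement section states separately that they are blinded.

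4. **How much of the trial is affected.** The plan has 22 + 22 = 44 participants, each tested 3 times. Two of the tests follow the bout, so with no dropout 44 × 2 = 88 of 44 × 3 = 132 planned assessments are made by participants who know their arm. For the other 44, the pre-tests, the article does not settle what the participant knows.

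5. **The pre-test.** Assignment follows eligibility screening, which consists of a medical history questionnaire and the PAR-Q. The pre-test comes later, immediately before the bout. There is thus an interval in which an allocation exists and the pre-test is still to be done. The article says that the sequence is held in sealed envelopes and concealed until completion, but not what is completed. If the end of the trial is meant, it cannot apply to someone who has been sent to the pool. When the participant is told is therefore not fixed.

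**The case against.** The best defence is that blinding is meant in a looser sense: participants might not know which environment is expected to do better. That is possible, but the text says allocation, and nothing in the article restricts the claim to the hypothesis. If that is the meaning, the wording still has to change.

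A second defence is that relabelling alters no data: nobody can be blinded to water, both arms receive the same active task, and hand contact, foot-off and foot contact are timed by force plates and a force-sensitive resistor after a sudden release. This stands as a limit on the likely size of any bias in the timed outcomes. It does not make the stated property true.

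A reader might infer more than the documents support:

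- **That the baseline is contaminated.** The article describes assignment before the pre-test, not disclosure, and refers to sealed envelopes. Nor would a disturbed baseline necessarily pass one for one into the result. If a pre-test were shifted by δ, an unadjusted change would move by −δ, but the Statistical analysis section enters baseline values as covariates if baseline differences occur, and the shift would then be −bδ, with b the regression slope, which need not be 1.
- **That the assessor or raters are unblinded by wet hair or clothing.** The article is silent on drying and clothing, and the water reaches only the xiphoid process. A compulsory change of clothes would also pull against a post-test defined as immediate.
- **That the satisfaction, difficulty and safety ratings distort the trial's outcomes.** They are self-reports by people who know their arm, but they are not among the seven dependent variables in the Statistical analysis section.
- **That the article expressly claims protection against performance bias.** It does not use the term. Such protection is only implied by the label and the statement about participants.

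**Conclusion.** The concern holds for participant blinding. The label in the Abstract and in Study design and setting, and the participant claim in Blinding, are wrong as written: none of the 44 planned participants can be blind to allocation once the session has begun. The conclusion rests only on the article's own description of the two environments and needs no outside source.

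It does not extend to the assessor/analyst or the video raters, whose blinding remains feasible. The direction and size of any expectation effect on post-intervention and follow-up results cannot be derived from the article. Disclosure before the pre-test is a risk left open by the stated order of events and is not a demonstrated bias.

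**What to change.** 1. In the Abstract and in Study design and setting, replace the double-blinded label, and in Blinding replace the participant claim, with: *assessor- and rater-blinded; participants and instructors not blinded*. Add *participants blinded to the study hypothesis* only if that is true.
2. State that expectation effects are possible and will be considered when post-intervention and follow-up results are interpreted.
3. In Randomization and allocation concealment, state that the participant is told the allocation only after the pre-test is completed, and say what completion means in the sentence about the envelopes.

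Items 1 and 2 cost wording and a less favourable label. Item 3 costs one sentence and, if it is not already the practice, having the envelope opened between the pre-test and the bout. The article gives no interval between randomisation and the session, so the scheduling effort cannot be stated. Sample size, outcomes, intervention and analysis are unchanged. Because Data management and confidentiality commits the investigators to communicating important modifications to the registry and the journal, the corrected description should go to both.
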